## Abstract

**Background:**

The publication of protocols by medical journals is increasingly becoming an accepted means for promoting good quality research and maximising transparency. Recently, Finfer and Bellomo have suggested the publication of statistical analysis plans (SAPs).The aim of this paper is to make public and to report in detail the planned analyses that were approved by the Trial Steering Committee in May 2010 for the principal papers of the PACE (Pacing, graded Activity, and Cognitive behaviour therapy: a randomised Evaluation) trial, a treatment trial for chronic fatigue syndrome. It illustrates planned analyses of a complex intervention trial that allows for the impact of clustering by care providers, where multiple care-providers are present for each patient in some but not all arms of the trial.

**Results:**

The trial design, objectives and data collection are reported. Considerations relating to blinding, samples, adherence to the protocol, stratification, centre and other clustering effects, missing data, multiplicity and compliance are described. Descriptive, interim and final analyses of the primary and secondary outcomes are then outlined.

**Conclusions:**

This SAP maximises transparency, providing a record of all planned analyses, and it may be a resource for those who are developing SAPs, acting as an illustrative example for teaching and methodological research. It is not the sum of the statistical analysis sections of the principal papers, being completed well before individual papers were drafted.

**Trial registration:**

ISRCTN54285094 assigned 22 May 2003; First participant was randomised on 18 March 2005.

## Update

### Background

#### **
*Publication of statistical analysis plans*
**

The review and publication of study protocols by medical journals are increasingly becoming an accepted means for promoting good quality research and maximising transparency. Since 1997 *The Lancet* has actively invited investigators to submit their protocols to the journal for peer review, offering a provisional commitment to publish the principal results where their criteria are satisfied [1-4]. Since 2001, following a call from Chalmers and Altman [5], *BioMed Central* has been inviting trialists and other researchers to publish their full protocols online [6]. *The British Medical Journal*, while not offering peer review or publication as yet, has required authors to submit trial protocols with their manuscripts since January 2005, making them available to editors and reviewers as additional documentation [7]. More recently, calls have been made for the publication of other key trial documentation. Chan, for instance, has argued the case for public access to regulatory agency submissions [8]. In an editorial for *Critical Care and Resuscitation*, Finfer and Bellomo suggested the publication of statistical analysis plans [9]. The plans for the NICE-SUGAR (Normoglycaemia in Intensive Care Evaluation and Survival Using Glucose Algorithm Regulation) and RENAL (Randomised Evaluation of Normal versus Augmented Level of Replacement Therapy) studies [10,11] were published in the same issue.

A statistical analysis plan (SAP) is defined within the International Conference on Harmonisation’s guidance on the statistical principles for clinical trials (ICH E9) as ‘a document that contains a more technical and detailed elaboration of the principal features of the analysis described in the protocol, and includes detailed procedures for executing the statistical analysis of the primary and secondary variables and other data’ [12]. According to ICH E9, the statistical analysis plan should be pre-specified, completed after the protocol has been finalised but reviewed and possibly updated as a result of a blind review of the data carried out after the completion of data collection. It is suggested that details of the primary analysis should be clearly distinguished from those of supporting analyses and that the methods for handling missing data, outliers and multiplicity be described [12]. While the statistical analysis plan is clearly an important document, at present it is rarely made available to people outside of the study.

There are many reasons why study-specific statistical analysis plans should be published in full, with electronic journals offering the greatest potential for this to be commonplace. Due to space constraints, the paper providing the principal results often contains only a very limited description of the analyses that were planned or carried out. If the study protocol is published, further information is likely to be available. However, this is often insufficient to enable full replication of the analyses. The statistical analysis plan complements both the protocol and the principal paper by providing a systematic and comprehensive description of the planned analyses, taking into consideration any relevant methodological or clinical developments that may have arisen since the study’s inception. Its publication enables any changes to the original plan to be laid out, increasing the scientific rigour and transparency with which the principal analyses are currently reported.

Maximum transparency regarding what decisions were made *a priori* could be achieved by publishing the statistical analysis plan, which has been approved by the Trial Steering Committee (TSC), before the results of a study are known. The final analyses reported may differ from those planned, allowing for *post*-*hoc* analysis where it is indicated (as Finfer and Bellomo [9] have noted), reporting alternative methods if statistical models do not converge, and omitting planned analyses that are superseded, redundant, or no longer of interest. Assessment of the validity of the analyses, reporting and consequent interpretation would also be made easier by the increased visibility of selective or misreporting. This may, in turn, encourage more balanced, accurate and complete reporting of results and ultimately help to raise the standard of trial analyses. Peer review has particular advantages, as it encourages dialogue, the quality of which is likely to be improved by the level of detail given. Knowledge of this added scrutiny should, in turn, act to promote the quality of the submitted plan. This process would be especially valuable if the research is anticipated to generate debate or if it might have a large impact on clinical practice.

The benefits of publication go beyond those specific to the study. Making statistical analysis plans accessible will help future statisticians and other researchers design and analyse better studies. This is because each study throws up different issues, often more complex than the standard textbook ones. Publishing details of the ways in which different groups choose to address these helps to generate discussion and could also promote greater communication and collaboration between methodologists, applied statisticians and researchers.

#### **
*The PACE trial*
**

The rationale for the trial is outlined in the protocol [13] and main clinical paper [14]. To be brief, chronic fatigue syndrome is characterised by chronic disabling fatigue in the absence of an alternative diagnosis, present in 0.2 to 2.6% of the population. The National Institute for Health and Clinical Excellence (NICE, UK) recommends two treatments: cognitive behaviour therapy (CBT) and graded exercise therapy (GET), but patient organisations recommend a third treatment: adaptive pacing therapy (APT). A definitive randomised trial was therefore needed to compare all three treatments with specialist medical care (SSMC) and to compare the established treatments (CBT, GET) against the new treatment (APT).

The objective of this paper was to make public and report in detail the planned analyses for the principal papers of the PACE (Pacing, graded Activity, and Cognitive behaviour therapy; a randomised Evaluation) trial, using the template statistical analysis plan developed by the Mental Health and Neuroscience (MH&N) Clinical Trials Unit based at the Institute of Psychiatry. These planned analyses were written with a view to publication and are reproduced almost as they were approved by the Trial Steering Committee (Version 1.2 dated 2 May 2010) prior to database lock. The changes from the original document were editorial clarifications suggested by reviewers and editors for which we are most grateful; these changes in no way alter the strategy for analysis. The SAP supplements the published protocol [13], the main clinical [14] and health economics [15] papers and the authors’ reply [16] to a selection of correspondence published by the Lancet [17-24]. They also provide an illustration of the planned analyses of a complex intervention trial taking into account the impact of clustering by care providers, where multiple care providers are present for each patient in some but not all arms of the trial. Details of the statistical aspects of multiple therapist-per-patient designs are published elsewhere [25].

### Statistical analysis plan

#### **
*Introduction*
**

##### 

**Purpose and scope of statistical analysis strategy** This document details the presentation and analysis strategy for the principal paper(s) reporting results from the PACE Trial. It is intended that the results reported in these papers will follow the strategy set out here; subsequent papers of a more exploratory nature will not be bound by this strategy but will be expected to follow the broad principles laid down for the principal papers. The principles are not intended to curtail exploratory analysis or to prohibit sensible statistical and reporting practices, but they are intended to establish the strategy that will be followed, as closely as possible, when analysing and reporting the trial. Reference was made to the published trial protocol [13], ICH Guidance on Statistical Principles for Clinical Trials (E9) [12], CPMP points to consider on multiplicity [26], and CONSORT guidelines for the reporting of harms [27] and for non-pharmacological treatment trials [28].

##### 

**Analysis strategy group** The Statistical Analysis Strategy was developed by the PACE Analysis Strategy Group whose members were:

– [name] (Chair, Principal Investigator)

– [name], [name], [name] and [name] (Statisticians)

– [name] (Health Economist)

– [name] and [name] (Principal Investigators)

– [name] and [name] (Trial Managers)

##### **
*Convention*
**

Throughout this Statistical Analysis Strategy the four individual randomised interventions are referred to as APT (adaptive pacing therapy *plus* standardised specialist medical care), CBT (cognitive behaviour therapy *plus* standardised specialist medical care), GET (graded exercise therapy *plus* standardised specialist medical care), and SSMC (standardised specialist medical care *alone*).

Unless stated otherwise ‘intervention’ refers to the four randomised interventions (group), and ‘therapy’ refers to APT, CBT, or GET. ‘Treatment’ is used more generally and embraces all forms including drugs.

The anchoring date for visits and assessments is randomisation; thus 24 weeks refers to 24 weeks from randomisation.

#### **
*Trial design and objectives*
**

##### 

**Study objectives** The PACE trial aims to answer the questions set out below under primary objectives, secondary objectives, and health economics objectives.

**Primary objectives**:

1. Is APT more effective than SSMC in reducing (i) fatigue or (ii) disability up to 52 weeks from randomisation?

2. Is CBT more effective than SSMC in reducing (i) fatigue or (ii) disability up to 52 weeks from randomisation?

3. Is GET more effective than SSMC in reducing (i) fatigue or (ii) disability up to 52 weeks from randomisation?

4. Is CBT more effective than APT in reducing (i) fatigue or (ii) disability up to 52 weeks from randomisation?

5. Is GET more effective than APT in reducing (i) fatigue or (ii) disability up to 52 weeks from randomisation?

**Secondary objectives**:

1. Is the pattern of results relating to the primary objectives replicated with the outcome as the participants’ self-rated clinical global impression change rating?

2. Do different interventions have differential effects on the two primary outcomes (that is, fatigue versus disability)?

3. Are the differences across interventions in the primary outcomes associated with similar differences in secondary outcomes?

Health economics objectives

The primary health economics objectives are as indicated below:

1. To compare care costs (including the costs falling to health service agencies, other agencies and also those borne by patients and their carers) and lost-employment costs up to 52 weeks for (i) CBT versus APT; (ii) GET versus APT; (iii) SSMC versus APT; (iv) CBT versus SSMC; (v) GET versus SSMC; and (vi) CBT versus GET.

2. To assess the relative cost-effectiveness and cost-utility of APT, CBT, GET, and SSMC (with costs based on health, social care, and informal care) up to 52 weeks.

The secondary health economics objectives are as indicated below:

1. To compare care costs (including the costs falling to health service agencies, other agencies and also those borne by patients and their carers) and lost-employment costs between randomisation and 24 weeks for (i) CBT versus APT; (ii) GET versus APT; (iii) SSMC versus APT; (iv) CBT versus SSMC; (v) GET versus SSMC; and (vi) CBT versus GET.

2. To assess the relative cost-effectiveness and cost-utility of APT, CBT, GET, and SSMC (with costs based on health, social care, and informal care) up to 24 weeks.

3. To describe the annual healthcare and societal costs at baseline and their association with clinical and demographic characteristics.

4. To describe and compare patterns of service utilisation up to 24 weeks and up to 52 weeks across the four interventions.

5. To identify patient characteristics which predict service costs for each intervention.

6. To identify patient characteristics which predict cost-effectiveness/cost-utility up to 24 weeks, and up to 52 weeks for each intervention.

Health economic hypotheses

The primary hypotheses are:

1. Health and other service costs do not differ between APT, CBT, and GET up to 24 weeks, and up to 52 weeks, but are all higher than the costs for SSMC.

2. Total (health and societal) costs up to 24 weeks, and up to 52 weeks, are highest for SSMC, followed by APT, and with no substantial difference between CBT and GET.

3. APT has better cost-effectiveness and cost-utility than SSMC up to 24 weeks, and up to 52 weeks.

4. Both CBT and GET have better cost-effectiveness and cost-utility than SSMC and APT up to 24 weeks, and up to 52 weeks, but their cost-effectiveness does not differ substantially.

The secondary hypotheses are:

1. Higher healthcare costs are associated with being female, being older and having comorbid conditions, particularly mood disorders and having other symptom-based diagnoses.

2. Higher total societal costs are associated with being male, being younger, having more severe physical disability, pervasive passivity (measured by actigraphy), certain illness beliefs, and having comorbid conditions, particularly mood disorders and having other symptom-based diagnoses.

##### 

**Outcome measures** The primary outcome measures will be:

1. Fatigue Chalder Fatigue Questionnaire (CFQ) (Likert scoring) [29].

2. Physical Disability SF-36 physical function (SF-36PF sub-scale, Version 2) [30].

Secondary outcome measures include safety outcomes, efficacy outcomes and health economics outcomes.

Safety outcomes are:

1. Serious deterioration (primary) defined as one or more of the following up to 52 weeks:

a. SF-36 physical function score diminishing by 20 or more points between baseline and any two consecutive assessment interviews.

a. Participant-rated CGI change score of “much worse” or “very much worse” at two consecutive assessment interviews.

a. Withdrawal from therapy (APT, CBT, or GET) later than 8 weeks due to participant’s reported worsening of their condition.

a. A serious adverse reaction.

2. Serious adverse events (includes serious adverse reactions and suspected unexpected serious adverse reactions).

3. Serious adverse reactions (includes suspected unexpected serious adverse reactions).

4. Non-serious adverse events (includes non-serious adverse reactions); numbers, proportions, and examples.

5. Withdrawals from the interventions.

The four components of ‘serious deterioration’ will be reported in addition to the composite outcome.

Efficacy outcomes are:

1. Participant rated Clinical Global Impression (CGI) [31] change category.

2. Anxiety measured by HADS-A subscale of the Hospital Anxiety and Depression Scale [32].

3. Depression measured by HADS-D subscale of the Hospital Anxiety and Depression Scale [32].

4. Six-Minute Walking Test [33].

5. Work and Social Adjustment measured by WSAS [34].

6. Participant Satisfaction (7-point item from very satisfied to very dissatisfied).

7. Centers for Diseases Control (CDC) Symptoms - Number of symptoms [35].

8. Jenkins sleep score [36].

A selection of the above efficacy outcomes will be reported in the primary paper as required to aid interpretation of the primary outcomes; other secondary outcomes will be reported in subsequent papers. The selection will, in part, be determined by space constraints.

Health economics outcomes are:

1. CSRI (service, societal, NHS and insurance/benefits costs) [37].

2. EuroQol [38].

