****):**

1. Adaptive pacing therapy + standardised specialist medical care (APT).

APT is based on the illness model of CFS/ME as a currently undetermined organic disease, with the assumption that APT can improve quality of life while not affecting the core disease other than providing the best conditions for natural recovery. APT is essentially an energy management approach, which involves assessment of the link between activity and subsequent symptoms and disability, using a daily diary, with advice to plan and pace activity to avoid exacerbations.

2. Cognitive behavioural therapy + standardised specialist medical care (CBT).

CBT is based on the illness model of fear avoidance, used in the three previous trials of CBT [39-41]. There are three essential elements: (a) assessment of illness beliefs and coping strategies; (b) structuring of daily rest, sleep, and activity, with a graduated return to normal activity; and (c) collaborative challenging of unhelpful beliefs about symptoms and activity.

3. Graded exercise therapy + standardised specialist medical care (GET).

GET is based on the illness model of deconditioning and exercise intolerance, used in the previous trials [42,43]. Therapy involves an assessment of physical capacity, negotiation of an individually designed home exercise programme with set target heart rates and times, and participant feedback with mutual planning of the next fortnight’s exercise programme.

4. Standardised specialist medical care alone (SSMC).

SSMC is given to all participants and includes visits to the clinic doctor with general, but not specific advice, regarding activity and rest management, such as advice to avoid the extremes of exercise and rest, as well as symptomatic pharmacotherapy. SSMC is standardised in the SSMC Doctor’s Manual. SSMC participants, like all other participants, will already have received the patient clinic leaflet (PCL). There will be no additional therapist involvement, and, in particular, there will be no diary monitoring with consequent advice.

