vi)	Serious deterioration: Component 3	Absent/present - Withdrawal from therapy more than 8 weeks after randomisation due to participant’s reported worsening of their condition
vii)	Serious deterioration: Component 4	Absent/present - A serious adverse reaction
viii)	Serious adverse events	Total number up to 52 weeks
ix)	Serious adverse reactions	Total number up to 52 weeks
x)	Adverse events	Total number and the proportion of participants having one or more up to 52 weeks
xi)	Withdrawals from intervention	No/yes; person responsible; reason; days from randomisation
xii)	Participant-rated CGI	Positive change; no change; negative change
xiii)	Anxiety (HADS-A)	Total (sum) of the anxiety items of the HADS (higher scores indicate more anxiety)
xiv)	Depression (HADS-D)	Total (sum) of the depression items of the HADS (higher scores indicate more depression)
xv)	Six minute walking test	Total number of meters walked - derived from the number of 10 meter lengths plus any partial distance
xvi)	Work and social adjustment	Total (sum) of all items (higher scores indicate less adjustment)
xvii)	Participant satisfaction	Very satisfied; moderately satisfied; slightly satisfied; neither; slightly dissatisfied; moderately dissatisfied; very dissatisfied
xviii)	CDC Symptoms (#)	Total (sum) of CDC symptoms 1 to 8
xix)	Jenkins Sleep Score	
xx)	CSRI - service costs	Total (sum) costs - derived by assigning costs (£) to each relevant item in the CSRI
xxi)	CSRI - societal costs	Total (sum) costs - derived by assigning costs (£) to each relevant item in the CSRI
xxii)	CSRI - NHS costs	Total (sum) costs - derived by assigning costs (£) to each relevant item in the CSRI
xxiii)	CSRI - insurance/benefit costs	Total (sum) costs - derived by assigning costs (£) to each relevant item in the CSRI
xxiv)	EuroQol	Item scores for Q1 to 5 will be weighted by utility values and summed to produce a total (this can range from −0.59 to 1, with 1 indicating full health)

Note: CDC, Centers for Disease Control; CGI, clinical global impression; CSRI, client service receipt inventory; DMEC, data monitoring and ethics committee; HADS, hospital anxiety and depression scale.

##### 

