**Definition of outcome measures (including trial periods)** The safety of the trial interventions will be assessed using the definition of serious deterioration that was developed for monitoring safety during the course of the trial (see Outcome Measures), participant-rated adverse events defined and recorded in accordance with the protocol, and withdrawals from intervention. Serious deterioration, defined at 52 weeks, will be the primary assessment of safety. Its four components will be reported separately to enable evaluation of their relative contributions. These draw on the two adverse outcomes defined in the protocol, namely negative change on either the participant-rated CGI or the SF-36 physical function scale defined at 12, 24 and 52 weeks.

Participant-reported adverse events, including comorbid conditions which started after randomisation, are reported in terms of their relatedness to the trial intervention (events versus reactions), seriousness (non-serious versus serious) and severity (mild, moderate, severe). In addition serious adverse events are reported by the above and by their expectedness (expected versus unexpected).

Three independent assessors, initially blinded to intervention, selected by AfME and approved by the TSC, will do the following:

1. review all non-serious adverse events to determining if any should be upgraded to serious adverse events (SAEs) (masked to intervention);

2. review all SAEs to agree their classification as such (masked to intervention);

3. rate the relationship of each SAE to the randomised interventions (unmasked to intervention) (to consider whether any might be serious adverse reactions (SAR) to an intervention or suspected unexpected serious adverse reactions (SUSAR)); and

4. review all SARs and SUSARs.

Assessors will work independently of each other during the both classification periods. Where there is disagreement, consensus will be sought. Where disagreement continues, a majority vote will be taken.

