##### **Descriptive statistics for outcome measures**

##### 

**Serious deterioration** Serious deterioration will be tabulated both overall and by its four components at week 52 by randomised intervention. Absolute risk difference tests will be performed between serious deterioration (yes or no) and randomised intervention.

##### 

**Adverse events** Adverse events will be tabulated separately by type (non-serious adverse events, serious adverse events, serious adverse reactions and suspected unexpected serious adverse reactions), by time (weeks 0 to 12, weeks 12 to 26, weeks 26 to 52, and overall weeks 0 to 52), and by randomised intervention. Each table will include denominators showing how many participants were in the trial at each time point by randomised intervention. The numerator will indicate the number of affected participants, and an event rate will be provided indicating the events per unit of person time so as to capture events with recurrences.

The frequency of non-serious adverse events (non-serious adverse events and non-serious adverse reactions) per participant will be tabulated by randomised intervention.

All serious adverse events will be described individually: stating randomised intervention, participant identification number, centre, sex and age, investigator's reported term, preferred term, date of onset according to the date of the randomization, duration, number of SSMC sessions, number of therapist sessions (if applicable), action taken regarding the study intervention administration, use of a corrective treatment, outcome, relationship to the study intervention in the PACE clinician’s opinion and expectedness. Where the independent scrutineers have disagreed with the PACE clinician’s opinion, the scrutineers’ views only will be reported.

Deaths will be reported as described for a serious adverse event.

All adverse events leading to withdrawal (which constitute significant adverse events) will be summarised by randomised intervention, and whether the participant withdrew from the whole trial or intervention only.

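### One of the four components of serious deterioration cannot by design occur under SSMC, so the composite is not like for like in the three contrasts with SSMC

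*SAP article*

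**What the plan says.** - **Outcome measures, Safety outcomes.** Serious deterioration is "defined as one or more of the following up to 52 weeks", followed by four components. Component 3 is "Withdrawal from therapy (APT, CBT, or GET) later than 8 weeks due to" the participant's reported worsening. The other three are a sustained fall in SF-36 physical function, a sustained poor CGI rating, and a serious adverse reaction.
- **Table 3, component 3.** The derivation repeats the restriction: "Withdrawal from therapy more than 8 weeks after randomisation due to" reported worsening.
- **Convention.** In this SAP the word *therapy* "refers to APT, CBT, or GET". *Intervention* is the wider word that covers all four arms.
- **Randomised interventions, SSMC.** "There will be no additional therapist involvement".
- **Safety outcomes, Definition of outcome measures.** "Serious deterioration, defined at 52 weeks, will be the primary assessment of safety". The same section says that the four components are also reported separately.
- **Descriptive statistics for outcome measures, Serious deterioration.** "Absolute risk difference tests will be performed between serious deterioration (yes or no) and randomised intervention". The safety sample is the ITT sample, so all four arms enter.
- **Table 3, item xi.** Withdrawal from intervention, SSMC included, is recorded as "No/yes; person responsible; reason; days from randomisation".

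No version of the composite without component 3 is planned, and there is no caveat on contrasts with SSMC.

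**The concern.** Withdrawal because of reported worsening counts as serious deterioration in three arms and not in the fourth. The SAP accepts that participants can withdraw from SSMC (Departures from randomised intervention policy) and records when and why, but such a withdrawal never enters the composite.

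What is at stake is how the primary safety outcome is read for APT, CBT and GET against SSMC. A higher composite rate under a therapy could reflect more worsening, the extra route into the outcome, or both. Equal composite rates could conceal fewer events on the shared components in the therapy arm. The extra route pushes in one direction only, against the three therapies. Contrasts among APT, CBT and GET are unaffected, because component 3 is available in each of them.

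**Working it through.** The SAP states no expected rate or power for serious deterioration, so there is no figure to reproduce. The asymmetry follows from the definitions. The arithmetic below only shows how large it could be.

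**Step 1: definitions side by side.** The parenthesis in the outcome definition names APT, CBT and GET. The Convention gives the same meaning to Table 3's shorter wording. The same list of safety outcomes has a separate item for withdrawals from the interventions, so the narrower word in component 3 is not loose drafting. The only way into component 3 for an SSMC participant is to receive a trial therapy off policy and then leave it. The SAP treats receipt of such a therapy as a departure from the randomised policy.

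**Step 2: inputs.**
- n per arm: 641 / 4 = 160.25, taken as 160 (SAP, number randomised).
- p0: risk of meeting component 1, 2 or 4, set equal in all arms. Assumed 2%, 5% or 10%.
- w: risk of component 3 in a therapy arm. Assumed 1% to 5%.
- o: share of component 3 cases who also meet another component. Assumed 0 or 50%.
- Two-sided alpha 0.05: stated in the SAP for the five efficacy comparisons, assumed here for safety.

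**Step 3: formulas.**
- Composite risk: p0 in SSMC; pT = p0 + w(1 − o) in a therapy arm.
- Definitional excess: d = w(1 − o), the proportion who meet component 3 only.
- SE0 = √[2·p̄(1 − p̄)/n], with p̄ = (p0 + pT)/2.
- SE1 = √[pT(1 − pT)/n + p0(1 − p0)/n].
- P(reject) = Φ[(d − 1.96·SE0)/SE1] + Φ[(−d − 1.96·SE0)/SE1].

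**Step 4: one case in full** (p0 = 5%, w = 5%, o = 0).
- pT = 10%, d = 0.05, p̄ = 0.075.
- SE0 = √(2 × 0.075 × 0.925/160) = 0.0295.
- SE1 = √((0.09 + 0.0475)/160) = 0.0293.
- P(reject) = Φ[(0.05 − 0.0577)/0.0293] plus a negligible second term = 0.40.
- Expected events: 16 against 8.

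**Step 5: range.**

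| p0 | w | o | Therapy v SSMC | Excess (points) | Ratio | P(reject) |
|---|---|---|---|---|---|---|
| 10% | 1% | 50% | 10.5% v 10% | +0.5 | 1.05 | 0.05 |
| 10% | 1% | 0 | 11% v 10% | +1.0 | 1.10 | 0.06 |
| 5% | 2% | 0 | 7% v 5% | +2.0 | 1.40 | 0.12 |
| 5% | 5% | 50% | 7.5% v 5% | +2.5 | 1.50 | 0.15 |
| 2% | 2% | 0 | 4% v 2% | +2.0 | 2.00 | 0.18 |
| 5% | 5% | 0 | 10% v 5% | +5.0 | 2.00 | 0.40 |
| 2% | 5% | 0 | 7% v 2% | +5.0 | 3.50 | 0.58 |

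Exact binomial enumeration with a Wald interval at p0 = 5% gives 0.111 for +2 points and 0.394 for +5 points, against 0.117 and 0.396 from the formula. The 0.58 in the last row rests on only 3.2 expected SSMC events (0.02 × 160), so it is approximate.

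**Step 6: can a reader undo this from the planned tables?** Suppose a therapy arm shows a composite of 10% and component 3 of 5%. The composite without component 3 is then 10% − 5%(1 − o). That is 5% with no overlap and 10% with complete overlap. The other components' counts may narrow this range, but marginal counts do not fix the value.

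**The case against.** The strongest reply is that the plan already exposes the problem. All four components are reported by arm, so component 3 would be visibly empty, or nearly so, in SSMC. Withdrawals from every intervention are also tabulated by arm, period and reason. This stands as real mitigation. It does not cure the problem, because the planned test is on the composite and Step 6 shows that the composite without component 3 cannot be recovered from marginal counts.

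A second reply is that leaving therapy because of worsening may be genuine harm, so the excess should not be called false. That also stands. The excess is an artefact only to the extent that comparable worsening goes uncounted in SSMC, and equal background risk is built into the calculation. The definitions alone show only that the composite cannot separate the two explanations. It is also fair to say that the definition inflates apparent harm of therapy rather than hiding it.

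A reader might go further and infer from Table 2 that its discontinuation-of-therapy column gives the therapy arms an extra occasion to meet components 1 and 2. The SAP does not support this. Those components require consecutive assessment interviews, and nothing says that a discontinuation visit is one. The visit-window rules let unscheduled data replace a missing planned visit rather than add to it. The DMEC algorithm that derives the outcome is not shown. The column also includes the doctor CGI and SSMC/therapy adherence, so it may not exclude SSMC.

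A reader might also link the ratios of 2 or more to the plan's promise to highlight any doubling in harms. That sentence sits in the paragraph on serious adverse events, and the SAP does not apply it to this composite.

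**Conclusion.** The point holds on the definitions. Apart from off-policy receipt of a trial therapy, component 3 cannot occur in SSMC. The composite therefore carries a definitional excess of w(1 − o) in each of APT, CBT and GET against SSMC.

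Its size is not established. Under the assumed ranges it runs from about +0.5 to +5 points, with rejection from about 5%, which is nominal, to 58%. Those probabilities assume that components 1, 2 and 4 are equally frequent in all arms. At the low end the effect on the test is negligible, and the SAP gives no rate that says where in the range the trial lies. The conclusion is that the planned contrasts with SSMC are not like for like. It is not that they would be materially misleading, nor that an excess under therapy would be false.

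**What to change.** For APT, CBT and GET versus SSMC:

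1. Derive and test a composite of components 1, 2 and 4, and base the safety comparison with SSMC on it. With component 3 left out, the built-in difference falls from w(1 − o) to zero, and the test returns to its nominal level when the shared components are equal across arms.
2. Report the full composite alongside, and state that it is not like for like with SSMC. Keep it as defined for contrasts among APT, CBT and GET.
3. If wanted, add a version that counts withdrawal for worsening from any randomised intervention, taken from Table 3 item xi, as a sensitivity analysis only. It equalises the wording but not the opportunity to withdraw. SSMC runs over 52 weeks and is given in every arm, whereas therapy runs for 23 weeks plus one booster session. Session requirements also differ: the cut-offs are three sessions for SSMC and ten for the therapies.

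The cost is a short change to the SAP text and one derived variable from data already recorded. There will be two versions of the outcome to explain. The version with components 1, 2 and 4 may also miss worsening that ended therapy but did not persist over two assessments, which is why the full composite should stay in the report.
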